**Anlotinib**			
**Abnormal liver function**	**Grade 1**	**Conduct follow-up as planned**	**8 mg****, ****qd**
	**Grade 2 (normal baseline)**	**Delay dose, strengthen guarantees the liver treatment and close monitoring of liver function once a week till < grade 2 within 2 weeks, and then continue anlotinib at a lower dose level**	**8 mg****, ****qod**
	**Grade 2 (abnormal baseline)**	**Strengthen guarantees the liver treatment and close monitoring of liver function once a week, continue anlotinib at an o initial dose**	**8 mg****, ****qd**
	**Grade 3**	**Delay dose, strengthen guarantees the liver treatment and close monitoring of liver function twice a week till < grade 2 within 2 weeks, till < grade 2 within 2 weeks, and then continue anlotinib at a lower dose level**	**8 mg****, ****qod**
	**Grade 4**	**Strengthen guarantees the liver treatment and close monitoring of liver function once/twice a week till < grade 2. Or have reasons for this issue**	**Discontinue anlotinib**
**Hypertension**	**SBP 120–139 mmHg or DBP 80–89 mmHg**	**Closely monitor, continue anlotinib at an initial dose**	**8 mg****, ****qd**
	**Asymptomatic grade 2 hypertension**	**Continue anlotinib at an initial dose. Start taking antihypertension medication or adjust its dose till blood pressure is effectively controlled (SBP < 140 mmHg or DBP < 90 mmHg) within two weeks, otherwise dose can be reduced as per investigator’s discretion**	**8 mg****, ****qd, or dose can be reduced as per investigator’s discretion**
	**Symptomatic grade 2 hypertension, or grade 3 hypertension**	**Discontinue anlotinib, and then start taking antihypertension medication or adjust its dose till blood pressure is effectively controlled within two weeks, continued anlotinib at an initial dose or a lower dose level**	**8 mg****, ****qd, or 8 mg****, ****qod as per investigator’s discretion**
**Abnormalities of bleeding and coagulation**	**Grade 1**	**Closely monitor, continue anlotinib at an initial dose**	**8 mg****, ****qd**
	**Grade 2**	**Discontinue anlotinib, till AE ≤ 1, and then continue anlotinib at a lower dose**	**8 mg****, ****qod**
	** ≥ Grade 3, or ≥ Grade 2 occurred twice (after discontinue or dose adjustment)**		**Withdraw from the pilot study**

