**Fluozopalib**			
**Grade 3 hematological toxicity**	**Grade 3 leukopenia not accompanied by fever**	**Discontinue fluozopalib till Grade ≤ 2 hematological toxicity, then fluozopalib was continued at an initial dose level**	**150 mg twice daily**
		**While grade 3 hematologic toxicity occurred again, discontinue fluozopalib till grade ≤ 2 hematological toxicity, then fluozopalib was continued at a lower dose level**	**100 mg twice daily**
		**While grade 3 hematologic toxicity occurred third time, discontinue fluozopalib till grade ≤ 2 hematological toxicity, then fluozopalib was continued at a much lower dose level**	**50 mg twice daily**
	**Grade 3 neutropenia not accompanied by fever**	**Discontinue fluozopalib till Grade ≤ 2 hematological toxicity, then fluozopalib was continued at an initial dose level**	**150 mg twice daily**
		**While grade 3 hematologic toxicity occurred again, discontinue fluozopalib till grade ≤ 2 hematological toxicity, then fluozopalib was continued at a lower dose level**	**100 mg twice daily**
		**While grade 3 hematologic toxicity occurred third time, discontinue fluozopalib till grade ≤ 2 hematological toxicity, then fluozopalib was continued at a much lower dose level**	**50 mg twice daily**
	**Grade 3 neutropenia accompanied by fever**	**Discontinue fluozopalib till Grade ≤ 2 hematological toxicity, then fluozopalib was continued at a lower dose level**	**100 mg twice daily**
		**While occurred again, discontinue fluozopalib till grade ≤ 2 hematological toxicity, then fluozopalib was continued at a much lower dose level**	**50 mg twice daily**
	**Grade 3 leukopenia or neutropenia accompanied by grade 2 thrombocytopenia/grade 2 anemia**	**Discontinue fluozopalib till Grade ≤ 2 hematological toxicity, then fluozopalib was continued at a lower dose level**	**100 mg twice daily**
		**While occurred again, discontinue fluozopalib till grade ≤ 2 hematological toxicity, then fluozopalib was continued at a much lower dose level**	**50 mg twice daily**
**Grade 4 hematological toxicity**		**Discontinue fluozopalib till Grade ≤ 2 hematological toxicity, then fluozopalib was continued at a lower dose level**	**100 mg twice daily**
		**While occurred again, discontinue fluozopalib till grade ≤ 2 hematological toxicity, then fluozopalib was continued at a much lower dose level**	**50 mg twice daily**

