**Grade 3 non-hematologic toxicity**		**Discontinue fluozopalib till Grade ≤ 1 hematological toxicity, then fluozopalib was continued at an initial dose level or a lower dose level**	**150 mg twice daily or 100 mg twice daily**
		**While occurred again, discontinue fluozopalib till grade ≤ 1 hematological toxicity, then fluozopalib was continued at a lower dose level**	**100 mg twice daily or 50 mg twice daily**
**Grade 4 non-hematologic toxicity**		**Discontinue fluozopalib till Grade ≤ 1 hematological toxicity, then fluozopalib was continued at a lower dose level**	**100 mg twice daily**
		**While occurred again, discontinue fluozopalib till grade ≤ 1 hematological toxicity, then fluozopalib was continued at a much lower dose level or discontinue**	**50 mg twice daily or discontinue**

*NCI CTCAE* National Cancer Institute Common Terminology Criteria for Adverse Events, *SBP* Systolic blood pressure, *DBP* Diastolic blood pressure

Take 1 capsule (8 mg) of anlotinib once daily on an empty stomach before breakfast. Stop 1 week after 2 consecutive weeks of oral administration, i.e. 3 weeks (21 days) as a treatment cycle. In case of missed dose, no additional dose will be given if the time for the next dose is confirmed to be shorter than 12 h. Patients with disease control (CR + PR + SD) and tolerable adverse effects will continue the dose.

For oral fluzoparib, it should be swallowed whole either after a meal or on an empty stomach (recommended after a meal). Take 3 capsules (150 mg) twice daily for 14 days, and 7 days of discontinuation as a treatment cycle (21 days). In case of a missed dose, the next dose should be taken normally at the scheduled time.

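### For a patient already on a reduced dose, the wording and mg columns of Table 2 can disagree, and the fluzoparib dose printed after a new grade 3 or 4 toxicity can exceed the current one

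*Protocol article*

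**What the plan says.** The Intervention section of the protocol article refers to Table 2 for dosing and dose-level changes, so the table is the operative rule. Fluzoparib starts at 150 mg twice daily. Three levels appear in the dose column: 150, 100 and 50 mg twice daily. In the rows that print a single dose, the action column calls these *initial*, *lower* and *much lower*.

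The fluzoparib rows that matter here are:

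- Third grade 3 leukopenia or neutropenia without fever: "While grade 3 hematologic toxicity occurred third time, discontinue fluozopalib till grade ≤ 2 hematological toxicity, then fluozopalib was continued at a much lower dose"; dose column 50 mg twice daily.
- First grade 4 haematological event and first grade 4 non-haematological event: restart at a *lower* level; dose column 100 mg twice daily in both.
- First grade 3 non-haematological event: "then fluozopalib was continued at an initial dose level or a lower dose level"; dose column "150 mg twice daily or 100 mg twice daily".
- Second grade 3 non-haematological event: "discontinue fluozopalib till grade ≤ 1 hematological toxicity, then fluozopalib was continued at a lower dose level"; dose column "100 mg twice daily or 50 mg twice daily".
- Second grade 4 non-haematological event: dose column "50 mg twice daily or discontinue".

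For anlotinib, the grade 3 liver row says "and then continue anlotinib at a lower dose level", and the dose column gives 8 mg every other day (qod). That is the only reduced anlotinib level the table spells out.

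No fluzoparib row mentions the dose in use when the event occurs.

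**The concern.** The action column describes a direction of change and the dose column prints an amount. The two must agree for a patient on 150 mg twice daily. They need not agree for a patient whom another row has already taken to 100 or 50 mg. A site following the words and a site following the figures could then give different doses to identical patients in a multi-centre trial, and the site following the figures could raise fluzoparib after a new severe toxicity.

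Repeated severe toxicity is foreseeable. The Background section cites grade 3 or higher anaemia in 25.1%, platelet decrease in 16.8% and neutrophil decrease in 12.6% of a fluzoparib-treated group, and says that anlotinib may raise fluzoparib blood levels.

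**Working it through.** The plan states no figure of its own to reproduce here. The check takes each fluzoparib row of Table 2 and divides the printed restart dose by each dose the patient might already be taking. A ratio below 1 is a reduction, 1 is no change, and above 1 is an increase. All doses are mg twice daily.

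| Row | Wording | Printed dose | From 150 | From 100 | From 50 |
|---|---|---|---|---|---|
| Grade 3 leukopenia or neutropenia, no fever, 1st | initial | 150 | 1 | 1.5 | 3 |
| same, 2nd | lower | 100 | 0.67 | 1 | 2 |
| same, 3rd | much lower | 50 | 0.33 | 0.5 | 1 |
| Grade 3 neutropenia with fever, 1st | lower | 100 | 0.67 | 1 | 2 |
| Grade 3 leukopenia or neutropenia with grade 2 thrombocytopenia or anaemia, 1st | lower | 100 | 0.67 | 1 | 2 |
| Grade 4 haematological, 1st | lower | 100 | 0.67 | 1 | 2 |
| 2nd occurrence in each of the last three categories | much lower | 50 | 0.33 | 0.5 | 1 |
| Grade 3 non-haematological, 1st | initial or lower | 150 or 100 | 1 or 0.67 | 1.5 or 1 | 3 or 2 |
| Grade 3 non-haematological, 2nd | lower | 100 or 50 | 0.67 or 0.33 | 1 or 0.5 | 2 or 1 |
| Grade 4 non-haematological, 1st | lower | 100 | 0.67 | 1 | 2 |
| Grade 4 non-haematological, 2nd | much lower, or stop | 50 or 0 | 0.33 or 0 | 0.5 or 0 | 1 or 0 |

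From 150 mg, every row worded as lower or much lower gives a ratio below 1, so words and figures agree. The disagreement appears only in the two right-hand columns.

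Those columns can be reached from within the table:

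1. Three episodes of grade 3 neutropenia without fever take the dose 150 → 150 → 100 → 50. A first grade 4 haematological event then meets a row worded as lower that prints 100, and 100/50 = 2.
2. Two episodes of grade 3 neutropenia with fever take the dose 150 → 100 → 50. A first grade 4 non-haematological event then prints 100, and 100/50 = 2.
3. One episode of grade 3 neutropenia with fever takes the dose 150 → 100. A first grade 4 event of either kind then prints 100, and 100/100 = 1: worded as lower, but unchanged.
4. A first grade 3 non-haematological event resumed at 150, followed by two episodes of grade 3 neutropenia with fever, takes the dose 150 → 100 → 50. A second grade 3 non-haematological event then offers 100 (100/50 = 2) or 50 (50/50 = 1). The row is worded as lower and neither option is.
5. From 50 mg, a first grade 3 non-haematological event offers 150 (150/50 = 3) or 100 (100/50 = 2). This fits that row's words, which include the initial level, but both options are increases.

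Anlotinib shows a lesser form. A patient already on 8 mg qod with grade 3 liver toxicity is told to continue at a lower level, and the column gives 8 mg qod again, a ratio of 1.

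**The case against.** The strongest defence is that *lower* and *much lower* are names for fixed levels, 100 and 50 mg, rather than directions. The single-dose rows fit that reading, and on it their words and figures match. What is then missing is a general rule for combining toxicity categories, which a condensed article may leave to the full protocol. This softens the conflict in wording but does not remove the problem: a patient on 50 mg with a first grade 4 event is still printed 100 mg. Nor does the label reading hold throughout, because the second grade 3 non-haematological row uses the same word for both 100 and 50 mg. That row can instead be read as one step below each first-occurrence option, but then *lower* is relative there and fixed elsewhere, and the row still fails for a patient brought to 50 mg by another route.

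Other parts of the defence stand, and they limit the point. A reader might infer any of the following, and the article does not support them:

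- *That 150 mg after a first grade 3 non-haematological event contradicts the row.* It does not; the words allow the initial level.
- *That every patient with a second toxicity of a different kind is affected.* A patient resumed at 150 mg after a first grade 3 neutropenia without fever who then has a grade 4 non-haematological event is printed 100 mg, a true reduction (100/150 = 0.67).
- *That the grade 1 liver row returns a patient on qod to daily anlotinib.* The grade 2 and grade 3 liver rows themselves cover recovery to below grade 2 and give 8 mg qod; the grade 1 row asks only for planned follow-up.
- *That the absence of a step below 50 mg in the haematological rows is an error.* It is at most an omission, and the general provisions on intolerable toxicity and investigator discontinuation remain.
- *That the dose-adjustment safety endpoint is distorted.* These patients have already been adjusted for toxicity and already count in that proportion.

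**Conclusion.** The point holds for patients already on a reduced dose who then meet a row printing an equal or higher one. For them the wording and mg columns of Table 2 disagree in the first grade 4 rows (haematological and non-haematological) and in the second grade 3 non-haematological row. The other rows that print 100 mg under the word *lower* share the pattern. The printed dose is up to 2 times the current dose where the words say lower, and up to 3 times where the words allow the initial level. The anlotinib case is minor: no change where the words say lower.

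The conclusion rests on reading Table 2 as printed, with no cross-category rule applied from elsewhere. The full protocol may contain such a rule; the finding is the disagreement inside this table, not the absence of that rule. The article gives no frequency for these sequences, so the ratios describe individual patients and not an average effect on the trial. Because a literal reading raises the dose after a grade 4 event, this should be settled as a matter of participant safety, even if few patients are involved.

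**What to change.** Reconcile the action and dose columns of Table 2. For each fluzoparib row, state what results for a patient whose current dose is 100 or 50 mg twice daily as well as for one on the initial dose, so that the words and the mg figure cannot point in different directions. Do the same for the anlotinib liver rows for a patient already on 8 mg qod. If the full protocol already settles how rows combine across toxicity categories, carry that rule into the table or refer to it there. Which dose or rule applies is for the sponsor to decide.

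The cost is a revision of the table's wording and notice of it to the sites. No extra patients, visits or procedures are needed, and the sample size is untouched.

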### Endpoints

The primary endpoint is Objective Response Rate. The secondary endpoints are progression-free survival, disease control rate, safety, duration of response, overall survival, quality of life. The safety endpoints are occurrence of adverse events, proportion of patients withdrawn due to adverse events, proportion of patients with dose adjustment due to adverse events. We will closely evaluate and monitor safety information in accordance with safety information evaluation and management practices during drug clinical trials. We will timely submit suspected and unexpected serious adverse reactions (SUSAR) reports through the pharmacovigilatory Electronic Transmission System (PV system), and timely submit safety update reports (DSUR) during the study and other potential serious safety risk information reports through the Drug Approval Center website. We will carry out risk monitoring, identification, assessment and control of safety information, timely discover existing safety problems or other risks, and promptly take measures of risk control and risk minimization, including general risk management measures (such as modifying clinical trial protocol), active suspension or termination of clinical trials.

Efficacy evaluation will be performed every two cycles (i.e., every 6 weeks) from 24 weeks after the first dose. All imaging data will be kept for patients with CR, PR, SD, and PD. If subjects discontinue the trial before the development of PD, follow up every 6 weeks for imaging (external hospital reports are acceptable) to observe whether the tumor progresses or take other anti-tumor therapies. Telephone or clinical follow-ups are acceptable.

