Recently, targeting DNA damage repair therapy including PARP inhibitors have shown therapeutic efficacy in SCLC and is considered to be a new potential treatment strategy for SCLC [3]. Although homologous recombination deficiency (HRD) or *BRCA1/2* gene mutations was not detected in SCLC very often, PARP inhibitors showed some antitumor activity in some preclinical and early clinical studies. However, the tumor suppressive activity of PARP inhibitor alone in SCLC is relatively low. PFS of UK STOMP study using olaparib as a maintenance therapy after first-line treatment for SCLC failed to be improved [4]. Therefore, PARP inhibitors in combination with other antitumor agents are emerging as a new clinical research strategy. One phase I/II clinical study published in Cancer Discovery in 2019 enrolled 50 SCLC patients given olaparib 200 mg bid × 7d combined with temozolomide 75 mg/m2 QD × 7d Q3W after the failure of previous standard therapy, and the result presented an ORR of 41.7%, a median PFS of 4.2 months and a median OS of 8.5 months [5]. Tumor response was confirmed in olaparib in combination with PD-L1 monoclonal antibody durvalumab in second-line and beyond in SCLC, especially two of three patients with inflammatory phenotype achieved PR [6]. Based on the results of ALTER1202 [7], the CFDA approved anlotinib for third-line and beyond treatment of SCLC, and lots of clinical studies of anlotinib in combination with other antitumor drugs for second-line and beyond treatment of SCLC are conducted, including anlotinib combined with chemotherapy (ChiCTR1500030474, ChiCTR1900028430, ChiCTR1900021983, NCT03823118), anlotinib combined with immunotherapy (NCT04192682, NCT04055792, NCT04234607).

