## Discussion

This study will provide evidence on efficacy and safety fluzoparib combined with anlotinib in ES-SCLC, which may be used as a candidate standard therapy.

A previous study demonstrated anlotinib has a high efficacy and safety profile in patients with advanced NSCLC [14]. A preliminary phase III efficacy and safety study enrolled 439 patients were randomized 2:1 to the treatment group and the placebo group, and the treatment group received oral anlotinib 12 mg/d. Respectively, the PFS of the treatment group and the placebo group were 5.37 months and 1.4 months, the OS was 9.63 months and 6.3 months, and the ORR and disease control rate in the anlotinib group were 9.18% and 80.95% significantly better than those in the placebo group (0.7% and 37.06%). Adverse events in the anlotinib group including hypertension, proteinuria and hand-foot syndrome were mild or moderate and controllable. As the first effective vascular targeting drug for the monotherapy of advanced NSCLC, anlotinib targets include VEGFR1/2/3, FGFR1/2/3 and PDGFRα/β. Compared with Bevacizumab, anlotinib has a more comprehensive neovascular targets to achieve efficient inhibition of neovascularization.

A multicenter, randomized, double-blind study ALTER1202 enrolled 11 study centers nationwide was designed to observe 120 patients with pathologically confirmed SCLC who had been treated with at least two prior systemic chemotherapy regimens. The main efficacy indicator is PFS [15].At WCLC 2018, it announced that the study met the primary study endpoint with the PFS of 4.1 m vs 0.7 m [HR:0.19 (95% Cl:0.12–0.32), *p* < 0.0001] and ORR of 4.94% vs 2.63%, respectively, in the anlotinib group (82 patients) and the placebo group (38 patients) for survival benefit. At ESMO 2019, the final OS data for ALTER1202 continued to be presented that 78% of patients had OS events and OS data were mature with a median OS of 7.3 m (6.1–10.3) vs 4.9 m (2.7–6.0) [HR: 0.53 (95% Cl:0.34- 0.81), *p* = 0.0029], 6-month OS rate of 63.9% vs 32.7%, and 1-year OS rate of 30.6% vs 13.1%. Subsequent subgroup analysis of the 68 patients showed that patients who had received prior radiotherapy achieved significantly prolonged median PFS by up to 4.8 months in anlotinib group compared to placebo group (5.49 months vs. 0.69 months, HR 0.14, *P* < 0.0001), and also significantly prolonged OS (9.49 months vs. 4.89 months, HR 0.46, P = 0.0388).

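### The stated start of tumour assessment, 24 weeks after the first dose, contradicts the treatment rules and, taken literally, would bias ORR downward and distort PFS

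*Protocol article*

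**What the plan says.** Everything here is in the protocol article.

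- Endpoints, on timing: "Efficacy evaluation will be performed every two cycles (i.e., every 6 weeks) from 24 weeks after the first dose". No other schedule of tumour assessment on treatment is given.
- Endpoints, on what depends on it: "The primary endpoint is Objective Response Rate". Of the secondary endpoints, PFS, disease control rate and duration of response also need scans.
- Intervention, text below Table 2, on cycle length: "i.e. 3 weeks (21 days) as a treatment cycle".
- Intervention: treatment runs until progression or intolerable toxicity, and "Patients with disease control (CR + PR + SD) and tolerable adverse effects will continue the dose".
- Table 1, withdrawal criteria: progression shown by imaging or by clinical features is a reason for withdrawal.
- Endpoints, after early stopping: patients who discontinue before progression are imaged every 6 weeks, with no 24-week delay stated.
- Table 1, inclusion criterion 6: minimum expected survival is 12 weeks.

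**The concern.** Read literally, the first scheduled evaluation comes after eight cycles. The article's other rules need tumour status well before that: nobody can be treated until progression, kept on treatment for CR, PR or SD, or withdrawn for imaging progression without an image. The rules and the schedule cannot all be followed as written. A patient who stops early could also be imaged sooner than one still on treatment.

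The entry criterion accepts an expected survival of half the wait to the first scan, and the small cell studies the article cites have median PFS below 24 weeks. Under the literal schedule, a response that begins and ends before week 24 has no scheduled scan to record it. ORR, the primary endpoint, then moves towards the proportion still in response at about week 24. Progressions that occur silently before week 24 are dated to the first scan, which distorts PFS, disease control rate and duration of response. The statistical section allows no imputation of missing data.

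**Working it through.** **The plan's own figure.** The Statistical analysis section gives a one-sided exact test at 5%, 80% power, a reference ORR of 9.4%, 22 evaluable patients, 25 after 10% dropout and 50 planned. Reading the hypotheses as 9.4% against 30%, the exact binomial with n = 22 and success at 5 or more responses gives alpha 0.0498 and power 0.835. The smallest n reaching 80% is 21 (alpha 0.0416, power 0.802), so 22 is sound. 22/0.9 = 24.4, rounded up to 25. The sample size is not at fault; what follows concerns how the response is observed.

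**Timing.** 24 weeks / 3 weeks per cycle = 8 cycles. 24 × 7 / 30.4375 = 5.52 months; 6 weeks = 1.38 months. A 6-weekly grid from the first dose would place scans at weeks 6, 12 and 18 before week 24.

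**Share of PFS events before the first scan.** Assume exponential PFS: P(event by t) = 1 − 0.5^(t/median). The medians come from the article: 4.2 months for olaparib plus temozolomide (Background: "an ORR of 41.7%, a median PFS of 4.2 months and a median OS of 8.5 months"), 4.1 months for anlotinib (Discussion: "PFS of 4.1 m vs 0.7 m", the first figure), and 5.49 months for the anlotinib subgroup with prior radiotherapy (Discussion).

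| Median PFS (months) | Before week 24 | Before week 6 | Of 50 patients, before week 24 |
|---|---|---|---|
| 4.1 | 1 − 0.5^(5.52/4.1) = 61% | 21% | 30 |
| 4.2 | 1 − 0.5^(5.52/4.2) = 60% | 20% | 30 |
| 5.49 | 1 − 0.5^(5.52/5.49) = 50% | 16% | 25 |

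**Effect on ORR.** The article gives neither time to response nor duration of response, so both are assumed: true ORR 30%, onset at week 6 or 12, exponential duration with median 3 to 6 months. The fraction still responding at week 24 is s = 0.5^(gap/median duration). The gap is 18 weeks (4.14 months) for onset at week 6 and 12 weeks (2.76 months) for onset at week 12. Apparent ORR = 0.30 × s.

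The article states no success threshold. For n = 50 the exact one-sided 5% rule against 9.4% is 9 or more responses (alpha 0.042). This rule is derived here. Power at a true 30% is 98%.

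| Onset | Median duration (months) | Still responding at week 24 | Apparent ORR | Power, n = 50 |
|---|---|---|---|---|
| Week 6 | 3 | 38% | 11.5% | 12% |
| Week 6 | 4 | 49% | 14.6% | 31% |
| Week 6 | 6 | 62% | 18.6% | 60% |
| Week 12 | 3 | 53% | 15.9% | 40% |
| Week 12 | 4 | 62% | 18.6% | 60% |
| Week 12 | 6 | 73% | 21.8% | 79% |

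The apparent ORR is about 12 to 22% and power about 12 to 79%. The calculation leaves out responses that first appear after week 24 and responses caught by imaging after early discontinuation; both would soften the loss.

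**The case against.** The strongest reply is that this is a slip of wording. The sentence itself speaks of every two cycles, and the treatment, continuation and withdrawal rules all imply earlier assessment. Words may have been lost from a schedule that changes at week 24. The article condenses a fuller protocol and the study-design figure is not shown. This stands as far as intent goes: the documents do not establish that the investigators planned no scan for 24 weeks. It does not remove the defect, because the article states a start time, gives no other, and does so in the sentence that fixes when the primary endpoint is measured.

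A reader might go further and infer that neither ORR nor PFS could be measured at all, or that radiological PFS could never fall below 24 weeks. The documents do not support either. Responses still present at week 24 would be recorded, clinical progression triggers withdrawal at any time, and patients who stop before progression are imaged every 6 weeks. These routes catch some early events, but selectively, by who stopped and why, so validity is still impaired.

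A reader might also say that the result would be compared with a topotecan ORR obtained under earlier scanning. The article does not give that study's scan schedule, so the point cannot be made.

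Finally, the PFS medians come from other regimens and, for anlotinib, from patients with at least two prior regimens. They are reference values for pretreated small cell disease and not the trial's benchmark. At 5.49 months the share of events before week 24 is half, so a majority rests on the shorter medians.

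**Conclusion.** The concern holds: the stated start of assessment is wrong as written and inconsistent with the Intervention section and the withdrawal criteria in Table 1. Taken literally, it biases ORR downward and lets the first scan date largely determine radiological PFS, with earlier progression caught only clinically or through imaging of early discontinuers.

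The contradiction needs no assumption. The PFS figures rest on exponential PFS and on medians borrowed from the cited studies. The ORR and power figures rest on the assumed onset and duration of response and on a success rule that the article does not state. They show the direction and a plausible range, and are not a forecast. Because the sentence governs the primary endpoint and is easily corrected, it should be fixed before the results are analysed or interpreted.

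**What to change.** Reconcile the assessment sentence in Endpoints with the treatment-duration and continuation rules in Intervention and the withdrawal criteria in Table 1. Correct the sentence along these lines: tumour assessment by RECIST 1.1 at baseline and every two cycles (6 weeks), counted from the first dose, with best overall response and PFS derived from all these scans. If week 24 was meant as the point at which the interval changes, say so in a separate sentence with the later interval.

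The cost is a one-sentence amendment, plus the scans at weeks 6, 12 and 18 if they were not already planned. If they were being done all along, only the text changes.
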